### Outcomes

2.9

The primary outcome of the trial is subjective relaxation, operationalized as the score on the “Calmness-Restlessness” subscale of the Multidimensional Mood State Questionnaire (MDBF) (14). This subscale directly assesses the participant's current state of inner calm vs. agitation, making it a suitable primary endpoint for an intervention aiming to increase relaxation. The MDMQ has demonstrated good internal consistency in prior research, with Cronbach's *α* between 0.86 and 0.94., depending on the population and setting (14). Primary analysis focuses on the change in this relaxation score from baseline (T0) to post-intervention (T1, week 6). The key comparison is between the combined Hypnosis + Essential Oil groups (1 and 2) and the control conditions (Hypnosis-only and Minimal Intervention). Several secondary outcomes will also be examined (all measured at T0, T1, and T2 using validated self-report instruments).

**Anxiety symptoms.** GAD-7 (13), a brief scale measuring the frequency of core GAD symptoms (worry, tension, etc.) in the past two weeks. It will indicate if the intervention reduces overall anxiety levels.

**Perceived stress.** PSS-14 (15) gauges the extent to which situations in life are appraised as stressful. We will see if participants report feeling less overwhelmed by stress after the intervention.

**Sleep quality.** PSQI (16) assesses sleep patterns and disturbances over the past month. Given the calming nature of the intervention, improvements in sleep quality (lower PSQI scores) are expected in the active groups, as anxiety and sleep are often linked.

**Well-being.** WHO-5 Well-Being Index (17), a short measure of positive mood and vitality. This captures any boost in general mental well-being or mood that might accompany stress reduction.

**Worry tendency.** PSWQ (20), German short form (PSWQ-d) measures trait worry severity. We will explore whether regular relaxation practice and perhaps improved coping reduce habitual worry levels in participants.

In addition to these standardized measures, intervention adherence and acceptance will be evaluated through a custom questionnaire at T1. This includes items about how often participants actually used the intervention as instructed (adherence), how easy or practical it was to integrate into daily life, any barriers encountered, and subjective perceived benefit or satisfaction with the intervention. These data will be reported descriptively to assess feasibility and user acceptance of this digital self-help approach. There is also an exploratory “worry context” checklist module: participants indicate the domains of life in which they currently experience the most worry such as work, relationships, health, and finances. While not an outcome *per se*, this can help describe the sample and potentially stratify whether the intervention effects differ by worry context.

From the Phase 2 conditioning period, the primary outcomes of interest remain subjective relaxation (MDBF Calmness) and VAS relaxation ratings. The critical comparison here is between matched vs. mismatched scent groups. If classical conditioning is successful and stimulus-specific, Groups 1 and 2, who get the same essential oil in Phase 2 as they had during conditioning, should show a greater relaxation response than Groups 5 and 6, who receive a different scent in Phase 2. In contrast, if any scent simply produces a general context effect, the mismatch groups might also relax, suggesting a more generalization or context effect rather than a specific conditioned link. Group 3 (hypnosis only) and Group 4 (minimal control) provide additional reference points at T2 such as Group 3 might show if any residual benefit of hypnosis persists without further sessions, and Group 4 indicates any natural change over 8 weeks without intervention.

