After six weeks of regular practice, Phase 1 concludes with the T1 assessment. Immediately thereafter, Phase 2 (weeks 7–8) begins, lasting two additional weeks. In Phase 2, participants no longer do the hypnosis sessions; instead, they engage in essential oil exposure alone every two days, continuing with the same schedule of thrice weekly exposure. During these sessions, they will inhale from the aroma stick, containing an essential oil, for a brief period (several minutes) but without any accompanying audio or hypnosis. The purpose is to test whether the essential oil itself can elicit a relaxation response after the conditioning in Phase 1. Some groups will receive the same oil in Phase 2 as they did during Phase 1 (matched condition), while others will receive a different oil (mismatched condition) to test the stimulus specificity of the conditioned response. No explicit relaxation exercise is given in this phase aside from the essential oil exposure. Participants still rate their mood before and after each essential oil exposure, as described below, to gauge any relaxation effect purely from the scent.

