### Timeline and assessments

2.7

The study duration for each participant is 6 weeks from start to finish and 8 weeks in total for participants from groups 1, 2, 5, and 6, with three main measurement points: baseline (T0), post-Phase 1 (T1 at 6 weeks), and post-Phase 2 (T2 at 8 weeks). Additionally, brief self-reports are collected throughout the intervention period to track immediate effects and adherence.

**Week 0: Baseline (T0).** Upon enrollment and after screening, participants complete an online baseline questionnaire battery before any intervention. This includes demographic information, the Multidimensional Mood State Questionnaire (MDBF) (14), the GAD-7 (13), the Perceived Stress Scale (PSS-14) (15), the Pittsburgh Sleep Quality Index (PSQI) (16), the WHO-5 Well-Being Index (17), and the Penn State Worry Questionnaire (PSWQ, German short form) (18). These instruments establish baseline levels of relaxation, anxiety severity, perceived stress, sleep quality, psychological well-being, and trait worry, respectively. A subset of participants in Berlin also undergoes baseline physiological recording (continuous electrocardiogram (ECG) and pulse). The intervention commences on the day following completion of the baseline assessment.

**Weeks 1–6: Intervention Phase 1.** Participants follow the assigned intervention every two days (∼3 times per week). Before each session, they are prompted to rate their current subjective relaxation level using a simple Visual Analogue Scale (VAS) (e.g., “How relaxed do you feel right now?” on a 0–100 scale). Immediately after each session, whether hypnosis with or without essential oil, they rate their relaxation again on the VAS. These pre-post VAS measures for every session provide a running check of acute changes in relaxation per session and allow analysis of trends. During this phase, Groups 1, 2, 5, 6 use their essential oil aroma sticks during the hypnosis sessions as instructed, while Group 3 uses no essential oil (hypnosis only) and Group 4 simply continues with minimal intervention. The study platform tracks adherence.

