**Week 6: Post-Intervention Assessment (T1).** At the end of week 6, after the last Phase 1 session, all participants complete the T1 online survey. This repeats the same set of standardized questionnaires as at baseline (MDBF Calmness-Restlessness, GAD-7, PSS-14, PSQI, WHO-5, PSWQ) to quantify changes in relaxation and secondary outcomes from T0 to T1. In addition, participants are asked an open-ended question about their experience by asking for example, “Please describe how you experienced the intervention.” and “How did you integrate the intervention into your daily life?” This qualitative prompt allows them to reflect on any perceived benefits, challenges, or routine they developed over the six weeks. The responses, entered as free text, will later be analyzed to gain insights into engagement, acceptability, and subjective impact. This approach further allows for the identification of unforeseen themes that may emerge in connection with the intervention. Participants in the physiology subgroup come into the lab around this time for their second physiological measurement.

**Weeks 7–8: Conditioning Phase 2.** These two weeks focus on testing conditioned relaxation. Participants in Groups 1, 2, 5, 6 now use the aroma stick alone every two days, without using the hypnosis audio. Group 1 continues with bergamot essential oil inhalation; Group 2 with lavender oil, both maintaining the same CS as in conditioning (match). Group 5 switches to lavender oil only, after being conditioned with bergamot, and Group 6 switches to bergamot oil only, after conditioning with lavender. Group 3 and Group 4 will not be followed up in this phase. As in Phase 1, participants in the active arms (1, 2, 5, 6) will record a VAS relaxation rating before and after each aroma exposure to quantify any immediate relaxation effect from the scent. This data will show whether merely inhaling the familiar essential oil produces a significant calmness boost, and whether that holds true only for the matching scent or also occurs with a mismatched scent).

**Week 8: Final Assessment (T2).** At the end of week 8, all participants, including groups 3 and 4, complete a T2 survey which again includes the MDBF Calmness-Restlessness subscale and the secondary outcome questionnaires (GAD-7, PSS-14, PSQI, WHO-5, PSWQ). This final measurement captures any further changes after the Phase 2 period.

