### Sample size calculation

2.11

The sample size was determined based on the primary outcome. The team conservatively anticipated a medium effect size for the group difference (Cohen's *f* ≈ 0.175, which corresponds roughly to d ∼0.35–0.40 in pairwise terms) given prior results based on the prior study on healthy individuals (11). Power analysis (*α* = 0.05 two-tailed, 1 − *β* = 0.80) for a one-way analysis of covariance (ANCOVA) with 4 groups and baseline as covariate, assuming the covariate explains ∼20% of variance, indicated needing about N ≈ 105 participants per group to detect *f* = 0.175. Allowing for up to ∼35% dropout, due to the fully online nature and 8-week duration, we decided to increase the target enrollment to ensure at least 105 completers per arm. Including the two extra groups for the conditioning test, the total planned sample size is *N* = 630 (105 × 6). This large sample will provide adequate power not only for primary comparison but also to explore secondary endpoints. Interim analyses are not planned; all data will be analyzed after study completion. The qualitative data from open-ended questions will be analyzed using deductive-inductive qualitative content analysis to identify patterns and themes in participants' experiences. We will integrate quantitative and qualitative findings in interpretation to understand the intervention's impact under consideration of multiple perspectives.

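### The adherence and feasibility report rests on a week-6 self-report questionnaire, which misses people lost before T1 and the Phase 2 exposures, although session records are already collected

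*Protocol article*

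**What the plan says.** Section 2.9 (Outcomes) names the instrument: "intervention adherence and acceptance will be evaluated through a custom questionnaire at T1". The adherence item asks participants how often they used the intervention as instructed. Other items cover practicality, barriers and satisfaction. The use of the answers is also stated: "These data will be reported descriptively to assess feasibility and user acceptance of this digital self-help approach".

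On timing, section 2.7 says: "At the end of week 6, after the last Phase 1 session, all participants complete the T1 online survey". Section 2.5.1 then says: "Immediately thereafter, Phase 2 (weeks 7–8) begins, lasting two additional weeks". The final survey is described as one in which participants "complete a T2 survey which again includes the MDBF Calmness-Restlessness subscale and the secondary outcome questionnaires"; the description names no adherence item.

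On expected losses, section 2.11 allows for up to about 35% dropout, "due to the fully online nature and 8-week duration, we decided to increase the target enrollment".

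The article also describes other records of use. Under weeks 1–6, section 2.7 states: "The study platform tracks adherence". The same section mentions brief self-reports during the intervention period that serve partly to follow adherence. It also describes relaxation ratings on a visual analogue scale (VAS) before and after each Phase 1 session and each Phase 2 aroma exposure. Section 2.5.2 adds an online checklist for preparing and refilling the aroma stick.

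**The concern.** The source named for the adherence figure depends on the behaviour it is meant to measure. In an unsupported online programme, people who stop using it are plausibly also those who do not return for the week-6 survey. A figure taken from T1 responders then describes those who stayed, while the feasibility statement is about the programme as offered.

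The timing adds a second gap. The questionnaire is completed before Phase 2 begins, so it cannot describe how often the scent-only exposures were carried out. Those exposures are the test of Hypothesis 2.1. A reader of a null matched-versus-mismatched result would want to know whether the exposures took place, and the named adherence source cannot say.

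This is a stated choice of source, not merely an omitted detail, and data already collected would serve better.

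**Working it through.** The article gives no adherence or feasibility figure, so there is none to reproduce. The check covers how far the named source reaches and how its error behaves.

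**1. Reach at T1.** Inputs from section 2.11: 630 participants (6 × 105) and dropout of up to about 35%. If the whole allowance fell before T1, 630 × 0.35 = 220.5, so about 220 participants would give no answer and about 410 (630 × 0.65 = 409.5) would remain. The allowance is a ceiling over eight weeks, so loss by week 6 may be smaller.

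**2. Reach into Phase 2.** Phase 1 lasts 42 days and Phase 2 lasts 14 (sections 2.1 and 2.5.1). At one session every second day that is 42/2 = 21 and 14/2 = 7, and 7/28 = 25% fall after the questionnaire. At three per week it is 18 and 6, and 6/24 = 25%. This applies to Groups 1, 2, 5 and 6 (4 × 105 = 420 randomised).

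**3. Error of a responder-only figure.** Let d be the share lost before T1, c the proportion of sessions done by T1 responders, and q the proportion done by non-responders.

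- Reported figure: c
- Figure for all randomised: (1 − d) × c + d × q
- Excess: c − [(1 − d) × c + d × q] = d × (c − q)

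Only the upper value of d comes from the article. The values of c and q, and the smaller values of d, are assumptions. With c = 0.80:

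| d | q = 0 | q = 0.20 | q = 0.40 | q = 0.80 |
|---|---|---|---|---|
| 0.35 | 28 points | 21 | 14 | 0 |
| 0.20 | 16 | 12 | 8 | 0 |
| 0.10 | 8 | 6 | 4 | 0 |

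For example, with d = 0.35 and q = 0.20, the figure for all randomised is 0.65 × 0.80 + 0.35 × 0.20 = 0.59, against a reported 0.80. The excess is positive whenever non-responders used the programme less than responders, and zero when use was equal.

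**4. The denominator.** Phase 1 frequency is described as every second day (21 sessions), as about three times weekly (3 × 6 = 18; section 2.7) and as roughly three to four times weekly (18 to 24; section 2.5.1). A participant with 18 sessions is 18/18 = 100%, 18/21 = 86% or 18/24 = 75% adherent, depending on which statement sets the denominator.

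**The case against.** The strongest reply is that the questionnaire is one instrument among several. Section 2.7 has self-reports and platform tracking of adherence, every Phase 2 exposure carries VAS ratings, and section 2.13 models the session ratings. Nothing says the questionnaire is the only source or that the other records will go unreported. A condensed article may also leave the derivation of an adherence rate to a fuller document. Much of this stands. A reader might infer that the trial holds no adherence data on early leavers or on Phase 2; the documents do not support that. The gap lies in the source named in section 2.9, not in data collection. What the reply does not remove is that section 2.9 ties the feasibility report to the questionnaire data and that no section routes the other records into it.

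Three further cautions hold:

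- A reader might take 35% dropout to mean that the questionnaire reaches at most 65% of participants. The allowance is an upper limit over eight weeks, so on the plan's own figure retention at week 6 would be at least about 65%. Someone who stops the sessions may also still answer T1.
- The session records are not fully objective. VAS entries are made by the participant, an entry does not prove inhalation, and the article does not say what the platform logs. Its tracking statement sits under weeks 1–6, so for Phase 2 the firmer support is the VAS entries.
- A session count cannot show whether use followed the instructions. The questionnaire item has value of its own.

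The differing frequency statements may be mere rounding, since every second day is 3.5 per week. They still yield different denominators.

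**Conclusion.** The point holds as a minor one. The source named for adherence and feasibility cannot reach participants lost before week 6, nor about a quarter of the scheduled sessions in the four oil arms. It is likely to overstate use. It is tempting to go further and say that feasibility is overstated by a definite amount, but the documents give neither loss before T1 nor the use made by responders and non-responders. At the 35% ceiling and an assumed 80% use among responders, the excess lies between 0 and 28 percentage points. With 10% lost before T1 it lies between 0 and 8. It vanishes if non-responders used the programme equally.

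The outcome is descriptive. The primary analysis and the Phase 2 comparison in section 2.13 do not use it. What is affected is the feasibility statement and the context for reading the conditioning result.

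**What to change.** In section 2.9, state that adherence will be reported from the platform and session records as sessions with entries divided by sessions scheduled. Report it for all randomised participants in Groups 1, 2, 3, 5 and 6 for Phase 1, and separately for Phase 2 in Groups 1, 2, 5 and 6. Count sessions after dropout as not done.

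Keep the T1 questionnaire beside this figure for use as instructed, practicality, barriers and satisfaction, and give the number of non-responders.

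Reconcile the session-frequency statements in sections 2.5.1 and 2.7 so that the denominator is fixed before the data are seen. Which frequency applies is for the investigators to settle.

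The cost is a few sentences and a small derivation from data already collected. The adherence figure will probably look less favourable.

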### Hypotheses

2.10

**Primary Hypothesis (H1—Efficacy).** After six weeks of intervention (T1), participants receiving self-hypnosis combined with essential oil inhalation (Groups 1 and 2) will demonstrate greater improvement in subjective relaxation, as measured by the Multidimensional Mood Questionnaire (MDBF), compared to participants receiving self-hypnosis without essential oil (Group 3) or a minimal-intervention control (Group 4).

**Primary Null Hypothesis (H0).** There are no differences between intervention groups in change in subjective relaxation from baseline to T1. **Primary Alternative Hypothesis (H1).** At least one intervention group differs from the others with respect to change in subjective relaxation from baseline to T1.

**Secondary Hypothesis 2.1 (Conditioned Relaxation).** In Phase 2, the essential oil alone will elicit relaxation in those groups that have consistent pairing in Phase 1. Specifically, participants in the CS-match conditions (Group 1 with bergamot, Group 2 with lavender) will show a significant increase in relaxation as measured by pre-post VAS and possibly MDBF from T1 to T2, when exposed to the essential oil alone, whereas those in CS-mismatch conditions (Group 5 and 6, who receive a different oil than used in training) will have smaller or no relaxation response. We hypothesize a stimulus-specific conditioning effect, meaning the relaxation response is tied to the particular essential oil used during training, not just any pleasant essential oil.

**Secondary Hypothesis 2.2 (Broader Psychometric Benefits).** The combined hypnosis + essential oil intervention will lead to greater improvements in other psychological outcomes compared to hypnosis alone or minimal intervention. We expect to see reductions in self-reported anxiety symptoms (lower GAD-7 scores), perceived stress (lower PSS-14), and worry (lower PSWQ-d) as well as improvements in sleep quality (lower PSQI) and overall well-being (higher WHO-5) in Groups 1 and 2 vs. Groups 3 and 4 at T1. This hypothesis posits that beyond immediate relaxation, the 6-week intervention confers broader mental health benefits (less anxiety and stress, better sleep and mood), echoing findings that combined mind-body interventions can positively affect multiple domains of functioning.

**Exploratory Hypothesis 2.3 (Moderators of Effect).** We will explore whether certain baseline factors moderate the intervention's effectiveness. Demographic factors like age, gender, or socioeconomic status might influence outcomes. For instance, it's possible that participants with higher initial anxiety, though still subthreshold, benefit more or less from the intervention, or that younger vs. older participants have different adherence rates. These analyses are exploratory and will be used to generate hypotheses for which subgroups respond best to this approach.

**Exploratory Hypothesis 2.4 (Physiological Effects).** We hypothesize that the combination of hypnosis and aromatherapy yields measurable physiological relaxation, reflected in increased parasympathetic activity or reduced sympathetic activity compared to hypnosis alone. In the laboratory subgroup, it is hypothesized that Group 1/2 (combined) will demonstrate larger increases in HRV, particularly high-frequency HRV, which is indicative of parasympathetic tone, and/or a greater reduction in heart rate and PWV from T0 to T1 than Group 3 (hypnosis only). This would suggest an additive effect of the essential oil on the body's relaxation response, consistent with objective evidence that an essential oil can modulate autonomic activity. However, given sample size limitations, this will be an exploratory outcome.

**Exploratory Hypothesis 2.5 (VAS Trajectory and Learning Effects).** By examining the VAS relaxation ratings collected before and after each session, we hypothesize that participants receiving the combined intervention will not only have larger acute relaxation gains per session on average than those in comparison groups, but they may also exhibit learning effects over time. A learning effect would manifest as gradually higher pre-session relaxation levels as weeks progress the participant's baseline state before each session improves, indicating they carry over some relaxed state or become more skilled at self-relaxation. We expect such effects might be most pronounced in those who undergo conditioning (Groups 1 and 2), potentially showing an upward drift in pre-session VAS scores and/or a plateau indicating habituation to relaxation. We will explore and graph these trajectories for insight into how the relaxation response develops with practice.

**Exploratory Hypothesis 2.6 (Qualitative Outcomes).** Through qualitative feedback, the open-ended responses at T1 and follow-up, we expect many participants to report positive experiences such as increased awareness of their mental well-being, incorporation of relaxation techniques into daily life, or newfound coping strategies. This approach also allows for the inclusion of potential negative experiences and challenges. We will qualitatively analyze these narratives for common themes. One exploratory question is whether participants experienced continued use of the essential oil or hypnosis techniques beyond the study and any long-term benefits or drawbacks. For example, some may report that the scent of lavender or bergamot now readily helps them calm down during stressful moments, indicating successful conditioning, or that the study motivated them to pay more attention to self-care. These rich personal insights will help assess the real-world impact and sustainability of the intervention beyond numeric scores.

